#### Sample size calculations

In this study, in order to evaluate the effect of three different therapies on upper limb motor function rehabilitation in patients with severe stroke hemiplegia, the upper limb part of the Fugl-Meyer rating scale (FMA-UE) is used as the main efficacy index. The subjects are divided into high frequency group, low frequency group and sham control group according to the principle of random control. According to the relevant literature and pre-experimental results, the average FMA-UE of each group was 11.4, 4.7 and 2.8, and the standard deviation was 1.4, 0.9 and 1.3, respectively. When the *α* of the bilateral test value is 0.05 and the power of the power is 0.9, according to the PASS15 software “Means—One WayDesigns (ANOVA)—ANOVA-Test—One-Way Analysis of Varianc F-Tests,” it is calculated that at least 9 cases need to be enrolled in each group, and considering the shedding situation, according to the calculation of 20% dropout rate, at least 12 cases are needed in each group, A total of at least 36 participants are required in the three groups (24).

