### Participants and eligibility

#### Enrollment criteria

The following are the inclusion criteria: (1) meet the diagnostic criteria for stroke: according to the “Guidelines for the Diagnosis and Treatment of Cerebral Hemorrhage in China (2019)” or “Guidelines for the Diagnosis and Treatment of Acute Ischemic Stroke in China (2018),” the diagnosis is confirmed by head CT/MRI imaging; (2)characteristics of stroke attack: initial unilateral onset, or no sequelae of neurological deficit left by previous stroke attacks; (3) vital signs and consciousness state: Vital signs are stable for ≥ 24 h, Glasgow Coma Scale (GCS) score = 15 points;(4) age range: 18–75 years old; (5) upper limb motor deficit: baseline Fugl-Meyer Upper Limb Motor Function Rating Scale (FMA-UE) score ≤ 26 points (suggesting severe motor impairment) (18); (6) informed consent: Voluntary written informed consent; (7) Recruiting patients within 1 week to 6 months after stroke.

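### Nine per group for 90% power does not follow from the stated means, SDs and one-way ANOVA, which together give 2 to 3 per group

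*Protocol article*

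**What the plan says.** All the ingredients stand in one paragraph of the protocol article, under Sample size calculations:

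- Endpoint: "the upper limb part of the Fugl-Meyer rating scale (FMA-UE) is used as the main efficacy index". The text does not say whether the values are end-of-treatment scores or changes from baseline.
- Inputs, in the order high-frequency (HF), low-frequency (LF), sham: "the average FMA-UE of each group was 11.4, 4.7 and 2.8, and the standard deviation was 1.4, 0.9 and 1.3, respectively". They are attributed to the literature and pre-experimental results.
- Two-sided alpha 0.05 and power 0.9.
- Method: the one-way ANOVA F-test in PASS 15.
- Result: "it is calculated that at least 9 cases need to be enrolled in each group", raised to 12 per group and 36 in total for 20% dropout.

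The Randomization and blinding section then sets enrolment at 36 on the strength of this calculation. The Enrollment criteria admit any patient with a baseline FMA-UE of 26 or less, between 1 week and 6 months after stroke.

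**The concern.** The printed means lie far apart relative to the printed SDs. HF and LF differ by 6.7 points, more than five pooled SDs. With separation of that size an F-test needs only a handful of patients, so 9 per group looks inconsistent with the paragraph's own inputs.

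The SDs themselves also raise a question. If the values are final FMA-UE scores, SDs of 0.9 to 1.4 are hard to reconcile with patients who enter anywhere from 0 to 26 points. If they are changes, the text should say so.

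This paragraph is the only justification for 12 per group. If the SD behind the 9 was really several points, the trial's power for the comparison named in its Objectives section (HF over the contralesional premotor cortex against LF over the contralesional motor cortex) is well below 90%. A reader who trusts the 90% figure could then take an inconclusive HF versus LF result as evidence of no difference.

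**Working it through.** **Inputs** (all from Sample size calculations): means 11.4, 4.7, 2.8; SDs 1.4, 0.9, 1.3; alpha 0.05; power 0.90; three equal groups.

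**1. Effect size**

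- Grand mean = (11.4 + 4.7 + 2.8)/3 = 6.3.
- Sum of squared deviations = 5.1² + 1.6² + 3.5² = 26.01 + 2.56 + 12.25 = 40.82.
- SD of the means = √(40.82/3) = 3.689.
- Pooled SD = √((1.96 + 0.81 + 1.69)/3) = √1.487 = 1.219.
- f = 3.689/1.219 = 3.03.

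**2. Attempt to reproduce the 9**

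Power = P(F′ > F crit), where F′ is noncentral F with df 2 and 3(n − 1) and noncentrality λ = n × 40.82/SD².

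| SD used | n per group | λ | Power |
|---|---|---|---|
| 1.219 (pooled) | 2 | 54.9 | 0.952 |
| 1.4 (largest) | 2 | 41.7 | 0.892 |
| 1.4 (largest) | 3 | 62.5 | 0.9997 |
| 1.219 (pooled) | 9 | 247.1 | above 0.9999 |

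The named test therefore needs 2 per group, or 3 with the largest SD. A simulation with the three unequal SDs agrees (0.944 at n = 2, 0.99997 at n = 3). Less natural choices do not reach 9 either. The root-sum-of-squares SD (2.11) gives 3, the three SDs added together (3.6) give 6, and the pooled SD with alpha 0.001 gives 4.

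The dropout step is correct: 9/(1 − 0.20) = 11.25, rounded up to 12.

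**3. What would give 9**

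- *The same F-test with a larger SD.* A common SD between about 4.72 and 5.05 makes 9 the smallest n with 90% power (0.900 at n = 9 for SD 5.05). That is 3.9 to 4.1 times the pooled SD.
- *A different test.* A two-sample t-test of LF against sham alone has a difference of 4.7 − 2.8 = 1.9, pair-pooled SD √((0.81 + 1.69)/2) = 1.118 and d = 1.70. Its power is 0.885 at n = 8 and 0.922 at n = 9. The match depends on the pair-pooled SD; with the three-group SD of 1.219, n = 9 gives 0.873 and 10 are needed.

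The document does not show which of these, if either, was used.

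**4. Power if the true SD is several points**

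The stated means are kept and the SDs are assumptions. Pairwise figures are unadjusted two-sided t-tests at 0.05.

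| Assumed SD | Omnibus, 9/group | HF vs LF (6.7), 9/group | LF vs sham (1.9), 9/group | Omnibus, 12/group | HF vs LF, 12/group |
|---|---|---|---|---|---|
| 5 | 91% | 76% | 12% | 97% | 88% |
| 6 | 77% | 60% | 10% | 89% | 74% |
| 8 | 51% | 39% | 8% | 65% | 50% |
| 10 | 34% | 27% | 7% | 46% | 35% |

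For scale, whole-number scores spread evenly over 0 to 26 have an SD of √((27² − 1)/12) = 7.8.

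**5. What the design can detect**

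With 9 evaluable per group, a pairwise t-test has 90% power at d = 1.63. That is 1.63 × 5 = 8.2 points at SD 5 and 1.63 × 8 = 13.0 points at SD 8.

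**The case against.** The strongest reply is that the mismatch runs in the safe direction. On the printed inputs 9 per group far exceeds 90% power, and the text says at least 9. Underpowering appears only when the printed SDs are replaced by values the document does not contain. This is correct, and the point should not be read as too few patients on the stated inputs. It does not rescue the paragraph, because 9 is presented as the calculated output for 90% power and those inputs do not produce it.

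The larger assumed SDs can also be challenged. The 7.8 benchmark describes raw scores, whereas the Data processing and analysis section plans a group-by-time analysis in which stable differences between patients largely drop out. With a raw SD of 7.8 and an assumed pre-post correlation of 0.8, the SD of change is 7.8 × √(2 × 0.2) = 4.9, close to the first row of the table. This stands as a caution. The rows for SD 8 and 10 suit an unadjusted comparison of final scores, and SD 5 is the more plausible figure if change is analysed. Even there, HF versus LF power is 76% with 9 per group and 88% with all 12 retained.

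Means of 2.8 to 11.4 also read naturally as improvements, in which case small SDs do not conflict with the entry criterion in the same way. That is fair, and it makes the unstated change-or-final question one of clarity, not proof that the SDs are wrong. Likewise, the LF-versus-sham source and the possibility that the SDs are standard errors are queries for the sponsor, not diagnoses.

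**Conclusion.** The concern holds. The stated means, SDs, alpha, power and test give 2 to 3 evaluable patients per group (6 to 9 in total), against the stated 9 (27 in total). No reasonable variant of the named F-test closes that gap, and nothing elsewhere in the article repairs it. At least one input, or the method, is misreported, so the 90% power claim cannot be traced. This conclusion rests only on figures printed in the protocol.

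Whether the trial is short of power cannot be settled from the document. It is not on the printed SDs. If the SD is near 5, the value at which the F-test does give 9, the omnibus test is adequate. HF versus LF then has 76% power at 9 per group, and LF versus sham has 12%. Larger SDs lower these further. This part depends on assumed SDs, on the stated means being right, and on 20% dropout occurring. It must be fixed because enrolment rests on this calculation alone.

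**What to change.** Keep 36 patients and rewrite the sample size paragraph:

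1. State whether the means and SDs are changes from baseline or end-of-treatment FMA-UE scores.
2. Go back to the source data and check whether 1.4, 0.9 and 1.3 are standard deviations or standard errors. Give the SD actually entered into the software.
3. Name the test actually powered. If it was a pairwise comparison, say which pair. HF versus LF is the natural choice given the Objectives section, though an omnibus three-group test is also legitimate if that is what is meant.
4. Restate what the design delivers: with 9 evaluable per group, 90% power for a pairwise difference of about 1.63 SD, translated into FMA-UE points at the confirmed SD.
5. If the 90% figure cannot be reproduced, delete it and present 36 as a feasibility-based size with the detectable difference above.

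The cost is one rewritten paragraph and, possibly, a less favourable power statement. No patients, assessments or visits are added.

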#### Randomization and blinding

Based on the sample size calculation, this study will enroll a total of 36 eligible subjects. Patients will be numbered sequentially according to their enrollment time and randomly assigned to one of three groups in a 1:1:1 ratio using a random number table. The study personnel responsible will number the patients and perform the randomization. Each numbered treatment protocol will be placed individually into an opaque, sealed envelope. Therapists will open the envelopes in numerical order and administer the treatment according to the corresponding protocol. The group codes will not be revealed until all analyses are completed. The sham stimulation group will use a mock device identical in appearance to the real equipment to replicate the look and acoustic noise of the active coil. The TMS operators will not be involved in trial design, assessment, or data analysis. Except for discussing discomfort or adverse effects, they will be prohibited from communicating any trial details with the subjects. All clinical assessors, behavioral therapists, data analysts, and other research staff will remain blinded to the group assignments (25).

#### Intervention

##### Treatment equipment

YRDCCY-I repetitive transcranial magnetic instrument (YRDCCY Medical Technology Co., Ltd.), equipped with 70 mm double-ring “8” coil (peak magnetic field intensity ≥ 2.2 T).

##### Target positioning process

When locating the target, the operator first determines the position of the CZ point on the scalp surface of the patient. According to the EEG 10–20 positioning system: Step 1: Measure the total length from the nasal root point to the external occipital carina point, record this length as L, start from the nasal root, move 50% of the L distance backward along this line, Cz1 point is at the midpoint of this midline. Step 2: Measure the total length of the left pre-auricular point passing through the top of the head to the right pre-auricular point, record this length as M, start from the left pre-auricular point, and move 50% M distance to the right along this line. The Cz1 point in the first step coincides or is extremely close, and this final intersection point is the Cz point. The CZ point corresponds to the anterior gyrus of the cerebral cortex about 5 cm lateral to both sides, and the plane of the midpoint of the coil is tangent to the surface of the scalp here, looking for the position that can trigger the maximum MEP amplitude of the contralateral abductor pollicis brevis (26), that is, the contralateral primary motor cortex (cM1), which is used as the target of rTMS in the low-frequency group. About 2.5 cm anterior to cM1 is cPMd (27), which is used as a target for rTMS in the high frequency group.

##### Treatment parameters

All three groups will be treated with rTMS in the same time with conventional drug therapy and rehabilitation training. During treatment, the patients will be placed in the lying position, and the “8” shaped coil will be placed near the tangent line of the scalp. Parameters of the low frequency group: The site is the M1 area of the cerebral cortex on the contralesional side, using 1 Hz, the intensity is 90% of the resting motor threshold, each sequence is 20s, 20 sequences will be repeated, intermittent for 1 s, and the total number of pulses is 1,200, once a day, 5 times a week, the course of treatment is 3 weeks. Parameters of high frequency group: PMd in the healthy cerebral cortex will be used as the target of high frequency group, at 5 Hz, the intensity is 90% of the resting motion threshold, each sequence is 6 s, 30 sequences will be repeated, intermittent for 6 s, the total number of pulses is 1,200, 5 times a week, and the course of treatment is 3 weeks. Parameters of the sham control group: The target and related parameters are the same as those of the high-frequency group, but the coil will be rotated 90 degrees to make it similar to the scalp of the participant and the discharge noise is similar to that of 5 Hz, so that the induced current in the brain will be minimized (28–30). The relevant time periods of the experiments are shown in Figure 2.

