**Methods and analysis:**

This study will be designed as a randomized, sham controlled clinical trial. Thirty-six patients with upper limb motor dysfunction after stroke will be included, and their Fugl-Meyer Upper Extremity Motor Function Rating Scale (FMA-UE) score will be ≤ 26 points. Subjects will be randomly assigned to the following three groups (*n* = 12/group): HF-rTMS: Treated with high-frequency (5 Hz) repetitive transcranial magnetic stimulation (rTMS) on the dorsal premotor cortex (PMd) on the contralesional side. Low-frequency group (LF-rTMS): Treated with low-frequency (1 Hz) rTMS on the primary motor cortex (M1) on the contralesional side. Sham control group: The stimulation target and parameter settings will be the same as those of the high-frequency group, but the coil will be placed perpendicular to the scalp plane. The intervention regimen will be rTMS treatment once daily, five times a week for 3 weeks. Outcome measures: Main outcome measures: Upper limb motor function, assessed by FMA-UE. Secondary outcomes: Barthel Index (BI), National Institutes of Health Stroke Scale (NIHSS). Exploratory indicators: fMRI data and motor evoked potential (MEP) parameters. All assessment data will be collected before and after the intervention.

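### The stated 1,200 pulses per session contradict the stated trains, which give 400 pulses in the low-frequency arm and 900 in the high-frequency arm

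*Protocol article*

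**What the plan says.** All the dosing figures are in the protocol article, Intervention, Treatment parameters.

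- **Low-frequency arm (contralesional M1):** "using 1 Hz, the intensity is 90% of the resting motor threshold", followed by "each sequence is 20s, 20 sequences will be repeated, intermittent for 1 s, and the total number of pulses is 1,200".
- **High-frequency arm (contralesional PMd):** "at 5 Hz, the intensity is 90% of the resting motion threshold", followed by "each sequence is 6 s, 30 sequences will be repeated, intermittent for 6 s, the total number of pulses is 1,200".
- **Sham arm:** no pulse total is printed. The text says "The target and related parameters are the same as those of the high-frequency group", with the coil rotated, so 1,200 applies by reference.

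The Abstract gives the schedule as "rTMS treatment once daily, five times a week for 3 weeks", which is 15 sessions. No other section gives a different train length, train count or pulse total.

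**The concern.** The number of pulses in an rTMS session is fixed by the frequency, the train length and the number of trains. The article prints all three for each active arm and then prints a total that they do not produce.

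Two things are at stake. The first is the definition of the treatment. Under Randomization and blinding, therapists open an envelope and deliver the regimen it names. An operator who sets the trains gives one dose; an operator who sets 1,200 pulses gives another, using trains that are not the published ones. Nothing in the article says which figure governs, so a reader cannot reproduce either regimen.

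The second is the comparison of the active arms. The Objectives section sets high-frequency stimulation of contralesional PMd against low-frequency stimulation of contralesional M1. Equal printed totals suggest that the arms are matched on pulses. If the trains are what is delivered, they are not matched, and the shortfall is larger in the comparator. The limitations paragraph does not mention unequal pulse counts.

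**Working it through.** **Formula.** Pulses per session = frequency (Hz) × train length (s) × number of trains.

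**Inputs** (all from Treatment parameters):

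| | Low frequency | High frequency (and nominal sham) |
|---|---|---|
| Frequency | 1 Hz | 5 Hz |
| Train length | 20 s | 6 s |
| Number of trains | 20 | 30 |
| Gap between trains | 1 s | 6 s |
| Stated total | 1,200 | 1,200 (sham by reference) |

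**Attempt to reproduce the stated total.**

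- Low frequency: 1 × 20 × 20 = 400, and 400 / 1,200 = 33%.
- High frequency: 5 × 6 × 30 = 900, and 900 / 1,200 = 75%.
- Ratio between the active arms: 900 / 400 = 2.25.

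**Check by stimulation time.**

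- At 1 Hz, 1,200 pulses need 1,200 s of stimulation. The trains provide 20 × 20 = 400 s, or 419 s elapsed with the 19 gaps.
- At 5 Hz, 1,200 pulses need 1,200 / 5 = 240 s. The trains provide 6 × 30 = 180 s.

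**Other readings tried.**

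| Reading | Low frequency | High frequency |
|---|---|---|
| One initial train plus the stated repeats | 1 × 20 × 21 = 420 | 5 × 6 × 31 = 930 |
| Gaps counted as stimulation | 1 × 21 × 20 = 420 | 5 × 12 × 30 = 1,800 |
| Weekly total (5 sessions) | 2,000 | 4,500 |
| Whole course (15 sessions) | 6,000 | 13,500 |

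None gives 1,200 in either arm.

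**Whole course.** The stated dose is 1,200 × 15 = 18,000 pulses in each active arm. The trains give 6,000 and 13,500.

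**Single changes that would restore 1,200.**

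- Low frequency: 1,200 / (1 × 20) = 60 trains of 20 s, or 1,200 / (1 × 20) = 60 s per train with 20 trains.
- High frequency: 1,200 / (5 × 6) = 40 trains of 6 s, or 1,200 / (5 × 30) = 8 s per train with 30 trains.
- Changing the frequency instead would need 1,200 / (20 × 20) = 3 Hz and 1,200 / (6 × 30) = 6.67 Hz. That contradicts the 1 Hz and 5 Hz given throughout the article, so the error lies in the trains or in the totals.

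**The case against.** The arithmetic cannot be disputed, so the case on the other side concerns consequence.

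- **The total may be the correct figure.** The same total appears in both arms, and one changed setting per arm restores it. The train settings may simply have been mis-transcribed, in which case the arms are matched and the 2.25-fold imbalance never occurs. This stands as a possibility, but the document does not settle it, so the imbalance is conditional on the trains being followed.
- **The comparison is already bundled.** The active arms differ by design in frequency, site and train pattern, and pulse matching is nowhere stated as an aim. Unequal pulses would be one more difference, not the only one. This also stands. It limits the harm but does not remove it, because the printed totals tell the reader that this difference is absent.
- **Each set of trains can be delivered.** That is true of the trains alone. Trains and total together cannot be met, so the regimen as a whole cannot be given as written.
- **Operators may all use one correct device program.** If so, the harm is confined to reporting and reproducibility. The article gives no such assurance, and equally gives no evidence that operators differ.
- **Sham is little affected.** The coil is turned to minimise induced current, so its pulse count is not an active dose, and sham stays matched to the high-frequency arm under either reading. This stands.

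Sample size, randomisation, outcomes and analysis methods are not touched by this point.

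**Conclusion.** The concern holds. In both active arms the stated total cannot be obtained from the stated frequency, train length and train count: 400 against 1,200 pulses per session at low frequency, and 900 against 1,200 at high frequency. Sham carries the high-frequency contradiction by reference.

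The finding rests only on the standard product of the three printed settings, and no alternative reading tried rescues the total. Which figure is wrong cannot be determined from the document. If the trains are right, the high-frequency arm receives 2.25 times the pulses of its comparator. If the total is right, the published train settings are wrong in both arms. Either way the dose of the intervention under test is not defined, so this must be corrected.

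**What to change.** 1. Check frequency, train length, number of trains, gap and total for each arm against the approved protocol and the program loaded on the device, and correct the paragraph so that the product equals the stated total. If 1,200 is the intended dose, the single-setting corrections shown in the working are the obvious candidates to check first.
2. State the pulse total for sham explicitly.
3. Record the pulses delivered at each session from the device.
4. If the reconciled totals differ between the active arms, state this with the objective and the limitations, and describe the high- versus low-frequency result as a comparison of whole regimens with unequal pulse counts.

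The cost is one corrected paragraph, one check of the device settings and one added data field. An ethics notification may be needed if the corrected settings differ from those approved.

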**Figure 2 fig2:**
[figure not shown]
Schedule of participant enrolment and assessments. FMA-UE, Fugl-Meyer assessment of upper extremity; MBI, Modified Barthel Index; MEP, Motor Evoked Potentials; NIHSS Scale, National Institutes of Health Stroke Scale.

### Outcome assessment

#### Primary outcome measure

The FMA-UE (Functional Motor Assessment Scale-Upper Extremity) will be used to assess motor function in the paralyzed upper extremity. A total of 10 items, including reflex activity, flexor muscle movement, extensor muscle movement, activity with common movement, dissociative movement, hyperreflexia, wrist stability, wrist movement, finger movement, coordination, and speed, are scored on a total of 66 points, with higher scores indicating milder dyskinesia (31).

### Secondary outcome

#### Scale and electrophysiological assessment

Modified Barthel index (MBI): including 10 activities closely related to daily living, such as eating, bathing, grooming, and dressing, which are used to assess the ability of daily living activities, the higher the score, the higher the independence of the patient’s daily life, and the score greater than 60 indicates that the patient is likely to be able to complete the activities of daily living and maintain a normal standard of living (32).National Institutes of Health Stroke Scale (NIHSS Scale): It includes a multi-faceted evaluation of the patient’s state of consciousness, language, sensory and motor function, which is used to evaluate the degree of neurological deficit, and the higher the score, the more serious the patient’s neurological impairment.Motor evoked potential (MEP): Before and after treatment, the upper limb MEP is measured for the patient, first the upper limb on the unaffected side and then the upper limb on the affected side; The electrode is recorded by electrodes attached to the abductor pollicis brevis muscle, the reference electrode is attached to the tendon, connected to the ground wire, and transcranial magnetic single stimulation is performed in the functional area of the opposite hand of the tested limb to observe the waveform and the patient’s limb. The latency and amplitude are recorded.

